### Secondary outcomes

Hip muscle function will be assessed with peak torque and RTD during isometric contractions for abduction and extension with a hand-held dynamometer (HHD) (ErgoFet HHD, Hoggan Scientific, Salt Lake City, Utah, USA). For each task, a participant will be positioned with the HHD and taken through a series of sub-maximal isometric contractions to allow for warm-up and acclimation. The warm-up will consist of contractions at 25, 50, 75 and 100% of their self-perceived maximal isometric contraction. Muscle function will consist of three 5 s maximal contractions with verbal encouragement. Participants will be provided with a 1 min rest period between trials and 3 min rest period between testing positions, with positions completed in a randomised order varied over sessions. We will collect an additional test trial if coefficient of variation is greater than 10% between the three peak isometric torque trials.^34^ We calculated inter-rater reliability of gluteal RTD (inter-rater ICC=0.66−0.78) and isometric hip strength (inter-rated ICC=0.83−0.88; intrarater ICC: 0.80−0.98) between the three site assessors during a training session. Hip muscle function will be collected preintervention and immediately postintervention.

The dynamometer will be calibrated before each testing session. Thigh and shank length will be measured in centimetres for the test limb. Hip abduction will be conducted in a side-lying position with the test limb positioned at 20° of hip abduction, slight external rotation and slight hip extension.^19^ The HHD will be placed on the lateral aspect of the limb, 5 cm proximal to the lateral epicondyle and secured with a stabilisation strap.^19^ A second stabilisation strap will be placed around the table and participant’s pelvis to minimise accessory motion. Hip extension will be conducted with the participant’s trunk on the table and their lower limbs off the table, with both the hip and knee at 90° of flexion. The HHD will be positioned against the treatment plinth and a stabilisation strap placed around the HHD and participant’s limb, aligned 5 cm proximal to the popliteal fossa. A second stabilisation trap will be positioned around the table and the participant’s pelvis to control accessory motion.

Frontal plane kinematics will be assessed during a single leg squat (SLS). Participants will wear tight-fitting clothes without shoes for the two-dimensional (2D) SLS assessment. Participants will complete an SLS on the pathological limb, with their contralateral limb flexed to 90° and arms placed across their chest.^35^ Participants will squat as low as possible and return to starting position.^35^ Coloured stickers will be placed on anatomical landmarks (sternum, bilateral anterior superior iliac spine (ASIS) and patella) to help quantify frontal knee, hip, pelvis and trunk kinematics. Video instructions will be provided to participants for sticker placement, camera placement and standardised squatting instructions. Squat speed will be standardised to a 2 s descend and 2 s ascend.^35^ Three practice trials will be provided before data collection, followed by 1 min rest, then three recorded trials. Researchers will assess and provide feedback on marker placement, camera placement and squatting performance at both baseline and immediate postintervention prior to data collection to improve accuracy. The feedback will serve as training for participants who will collect squatting performance remotely at the 6, 12, 18 and 24 months time points.

We will collect a global rating of change (GROC) score to quantify patient perceived change at all postintervention time points (immediate, 6- 12, 18 and 24 months). The GROC uses a single 7-point Likert-type scale with anchors of very much improved to very much worse. Also, each participant will be asked at the 6, 12, 18 and 24 months time points if they received additional care or treatment in the previous 6 months for their PFP. Those who have received care will be asked additional questions related to the type, reason and duration of care.

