### Data management

Force data will be normalised to body mass and converted to torque (Nm/kg). The mean of the three test trials will determine the peak isometric torque. RTD for each muscle will be calculated by the change in torque divided by a specific duration during the early (0–50 ms) and late (100–200 ms) phases. The RTD will be normalised to body mass and reported as Nm/kg/s. A custom MATLAB code will calculate RTD.^19^

We will measure frontal plane kinematics for the knee, hip, pelvis and trunk at both single leg stance and peak knee flexion of the SLS. Knee kinematics (knee-frontal plane projection angle (FPPA)) will be defined as the angle with bisecting lines between the ankle mortise, centre of the patella and the ASIS.^35^ Hip kinematics (hip-FPPA) will be defined as the angle between the centre of the patella, ipsilateral ASIS and contralateral ASIS.^35^ Pelvic drop will be defined as the angle between the horizontal line (aligned with the testing location), ipsilateral ASIS and contralateral ASIS. Trunk kinematics (lateral trunk motion) will be measured with the angle between a vertical line (aligned with the testing location), ipsilateral ASIS and manubrium sternum. There is good to excellent between session reliability (ICC=0.70−0.91) and intrarater (ICC _(2,1)_ = 0.75−0.90) in females with PFP.^35^ A single research team member, who will be blinded to group allocation, will measure the average of the three trials for all data points.

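### Knee-FPPA uses an ankle point that carries no sticker, and its peak-flexion reading depends on a squat depth that is neither fixed nor stated to be measured

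*Protocol article*

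**What the plan says.** The Secondary outcomes section of the protocol article lists the landmarks for the two-dimensional single leg squat: "Coloured stickers will be placed on anatomical landmarks (sternum, bilateral anterior superior iliac spine (ASIS) and patella". The Data management section defines knee-FPPA as "the angle with bisecting lines between the ankle mortise, centre of the patella and the ASIS". The other three angles use the patella, the two ASIS and the sternum, with a horizontal or vertical reference line where needed, so all their landmarks are on the sticker list.

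On how the squat is performed, the article says "Participants will squat as low as possible and return to starting position" and "Squat speed will be standardised to a 2 s descend and 2 s ascend". Tempo is fixed, but no target depth, depth record or depth adjustment is stated. Angles are read "at both single leg stance and peak knee flexion of the SLS".

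Participants are barefoot, researchers give feedback at baseline and immediately after the intervention, and one blinded reader averages three trials. At later visits the videos come from "participants who will collect squatting performance remotely at the 6, 12, 18 and 24 months time points". The Limitation section discusses remote marker and camera placement and the choice of the patella as a landmark, but neither the ankle point nor squat depth.

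**The concern.** Frontal plane kinematics is a named secondary outcome, and the study hypothesis expects it to improve more with STRIPE. In Table 2 hip rate of torque development stops at the postintervention visit, so kinematics is the only one of the two gluteal-function outcomes followed to 24 months.

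There are two separate weaknesses. First, the marker set does not supply a point that the knee angle needs, which adds reading error that a sticker would reduce. Second, the knee angle at peak flexion is read at whatever depth the participant reaches that day. Box 1 lists squatting among the pain-provoking tasks, so depth may change as pain changes. A projected frontal-plane angle grows with depth for the same sideways knee position, because thigh and shank appear shorter to the camera. A participant with less pain who squats deeper could then show a larger knee angle without any change in alignment.

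**Working it through.** **Definition against marker list**

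| Angle | Landmarks in the definition | Without a sticker |
|---|---|---|
| Knee-FPPA | ankle mortise, patella, ASIS | ankle mortise |
| Hip-FPPA | patella, both ASIS | none |
| Pelvic drop | both ASIS, horizontal line | none |
| Trunk | ASIS, sternum, vertical line | none |

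The gap applies to knee-FPPA at stance and at peak flexion.

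**The plan's own figure.** The article gives no angle SD, limb length, squat depth or reading error. The only stated figure that may bear on kinematics is power above 0.80 at d = 0.55 with N = 88 and baseline R² = 0.20. It reproduces: 0.55/√0.80 × √(44/2) = 2.88, and Φ(2.88 − 1.96) = 0.82 (0.81 with the noncentral t). It is not disputed.

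**Ankle point.** Error in the shank line = atan(e/L), where e is the side-to-side error and L the shank length. Both are assumed.

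| e | L = 36 cm | L = 40 cm | L = 44 cm |
|---|---|---|---|
| 0.5 cm | 0.8° | 0.7° | 0.7° |
| 1 cm | 1.6° | 1.4° | 1.3° |
| 2 cm | 3.2° | 2.9° | 2.6° |

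Averaging three trials helps if errors are independent: 1.4/√3 is about 0.8 degrees for 1 cm at 40 cm.

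**What measurement error costs in general.** If d = 0.55 is on an error-free scale, the observed effect is 0.55 × √ICC. With 44 per arm and R² = 0.20, power is 0.79 at the upper quoted between-session ICC (0.91), 0.68 at the lower (0.70), and 0.53 at an assumed 0.50. The share due to the missing sticker cannot be separated out.

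**Depth.** FPPA = atan(m/(S cos s)) + atan(m/(T cos t)), with medial knee displacement m, shank S = 40 cm, thigh T = 42 cm, and knee flexion split 40/60 between shank tilt s and thigh tilt t. All of these are assumed.

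| m | 60° flexion | 75° | 90° |
|---|---|---|---|
| 2 cm | 6.5° | 7.2° | 8.2° |
| 4 cm | 13.0° | 14.3° | 16.2° |
| 6 cm | 19.3° | 21.2° | 24.2° |

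A second set of assumptions gives similar values: both segments 40 cm, thigh/shank tilts 35/25, 47/33 and 53/37 degrees, m = 4 cm. It yields 13.3, 15.1 and 16.6 degrees at 60, 80 and 90 degrees of flexion.

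These are shifts within one person. The arm contrast depends on the difference between arms in depth change. In the second set the slope is (15.1 − 13.3)/20 = 0.09 to (16.6 − 15.1)/10 = 0.15 degrees per degree of flexion. An assumed 5-degree difference between arms would then move the contrast by 5 × 0.09 = 0.45 to 5 × 0.15 = 0.75 degrees.

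**The case against.** The strongest reply is that little of this is shown to matter. The stickers are described as an aid, not as covering every point. The ankle is visible, since "Participants will wear tight-fitting clothes without shoes for the two-dimensional (2D) SLS assessment", and one blinded reader locates it the same way in both arms, so the error costs precision and does not favour an arm. The article quotes between-session ICCs of 0.70-0.91, and the participant instructions are not shown. On depth, stance readings do not depend on it, no figure in the article links pain to depth, and holding medial displacement constant as depth changes is an assumption. Only knee-FPPA was modelled. Any bias arises only if depth change differs by arm. Under the hypothesis it would run against STRIPE, so it could hide a benefit rather than create one.

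Most of this stands and limits the point. It does not remove it. The list names specific landmarks and leaves out one that the definition requires. The ICCs are not stated to cover participant-filmed video, and good repeatability does not exclude a systematic shift when depth changes. Averaging three trials does not remove a depth shift common to all three. Depth changes after randomisation, so randomisation does not balance it.

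A reader might infer that the angles are not comparable across visits, or that depth is a problem of self-filming. The documents support neither. Comparability is not assured, which differs from being shown absent, and depth is equally free at the supervised visits.

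**Conclusion.** Two limited points hold. The marker list omits the ankle mortise that knee-FPPA requires, which adds avoidable reading error to that one angle: about 1.3-1.6 degrees per 1 cm on an assumed 36-44 cm shank, before averaging over trials. This is mainly a loss of precision.

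Squat depth is self-selected and not stated to be measured, so change in the peak-flexion knee-FPPA may combine alignment and depth. If pain relief and depth gain differ by arm, a kinematic benefit could be masked. The direction follows from the geometry for a fixed knee displacement. The size rests wholly on assumed limb lengths, tilts, displacement and depth change, and cannot be derived from the documents. Hip-FPPA, pelvic drop and trunk angles are outside the calculation.

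It might also be inferred that a matched-depth angle should replace the peak-flexion angle as the main measure. That is not supported: the peak-flexion method comes from cited work, whereas nothing in the documents validates a matched-depth reading. The outcome is secondary and no stated number is wrong.

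**What to change.** 1. Add a sticker at the midpoint of the ankle mortise to the marker set and to the participant video instructions. State that the ankle is read by eye on videos already recorded.
2. Keep the peak-flexion and stance angles as planned.
3. Measure squat depth from the same videos, for example as vertical ASIS drop relative to standing ASIS-to-ankle height, and report it by arm and visit.
4. Add a sensitivity analysis that reads knee-FPPA at matched depth: at the frame where the drop equals the participant's baseline drop, or at the shallower of the two drops if the later squat is shallower.

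The cost is one sticker, one line of instructions, and extra reading time for the single blinded reader. Where a later squat is shallower, the baseline video must be re-read at that depth, so the baseline covariate then varies by visit. This is acceptable in a sensitivity analysis but is a reason not to make it the main one. ASIS drop is a proxy that also moves with pelvic tilt, and on existing videos its scaling uses the eye-read ankle. Participants filmed before the change will have a small method difference. Blocked randomisation within site should spread this about equally over the arms. Treatment and visits do not change.

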### Data management

Force data will be normalised to body mass and converted to torque (Nm/kg). The mean of the three test trials will determine the peak isometric torque. RTD for each muscle will be calculated by the change in torque divided by a specific duration during the early (0–50 ms) and late (100–200 ms) phases. The RTD will be normalised to body mass and reported as Nm/kg/s. A custom MATLAB code will calculate RTD.^19^

We will measure frontal plane kinematics for the knee, hip, pelvis and trunk at both single leg stance and peak knee flexion of the SLS. Knee kinematics (knee-frontal plane projection angle (FPPA)) will be defined as the angle with bisecting lines between the ankle mortise, centre of the patella and the ASIS.^35^ Hip kinematics (hip-FPPA) will be defined as the angle between the centre of the patella, ipsilateral ASIS and contralateral ASIS.^35^ Pelvic drop will be defined as the angle between the horizontal line (aligned with the testing location), ipsilateral ASIS and contralateral ASIS. Trunk kinematics (lateral trunk motion) will be measured with the angle between a vertical line (aligned with the testing location), ipsilateral ASIS and manubrium sternum. There is good to excellent between session reliability (ICC=0.70−0.91) and intrarater (ICC _(2,1)_ = 0.75−0.90) in females with PFP.^35^ A single research team member, who will be blinded to group allocation, will measure the average of the three trials for all data points.

### Sample size

Power analysis for preintervention to postintervention differences was conducted with a Monte Carlo simulation involving 5000 replications of the data via the interval Monte Carlo simulation capabilities of Mplus V.8.6 for the multivariate analysis of covariance (MANCOVA) assuming: (1) standardisation of all analysis variables, (2) randomisation results in equivalent groups across the outcome variables at the baseline assessment, (3) homogeneity of covariate regression slopes (ie, 6-week postintervention outcome variables regressed onto their respective baseline assessment counterparts) will be ensured using parameter estimate equality constraints, (4) missing completely at random (MCAR) or missing at random (MAR) missing data were included in the simulation and ranged between 4.5% and 15.9% pairwise missing data (average=10%), (5) all six outcome variables were assumed to be intercorrelated at a medium effect size (ie, *r*_Pearson_=0.50), (6) baseline assessment scores for all six outcome variables, included as covariates, will explain (*R*^2^=0.20) 20% of 6-week postintervention variance, (7) maximum likelihood missing data handling will make N=88 available for analysis and (8) α=0.05 (two tailed). The power analysis question of interest was the smallest *d* incremental difference (*d*) at 6-week postintervention for STRIPE versus SOC participants detectable with power at 0.80. Power analysis results showed power would be >0.80 for any effect size difference between STRIPE and SOC participants of d>0.55.

Power analysis for the four postintervention (6, 12, 18 and 24 months) assessments was calculated with a Monte Carlo simulation involving 5000 replications of sample data using Mplus V.8.6 for the intercept-only structural equation model (SEM; growth curve model)^36^ assuming: (1) standardisation of all outcome variables at all time points, (2) *T*=five 6-month assessment time points (postintervention, 6, 12, 18 and 24 months follow-up), (3) all individual trajectories are horizontal but at different (intercept) levels, (4) randomisation results in equivalent groups, (5) intermittent missing outcome variable data will be MAR, increase every 6 months and monotonically from 1.1% at the first postfollow-up assessment to 9.1% at month 24 and (6) α=0.05 (two tailed). The dispositive power analysis question regarded statistical power levels to reject the treatment effect null hypothesis at various hypothetical sample sizes under the assumptions listed above. Power analysis results showed power would be >0.70 for any (intercept) effect size difference between STRIPE and SOC participants of d>0.55.

Power analysis for PFP recurrence was assessed with a binary logistic regression using the internal Monte Carlo simulation capabilities in Mplus V.8.6 assuming: (1) 50% of the STRIPE participants will have a PFP recurrence and 82% of SOC participants will have recurrence, (2) previous publications suggest PFP recurrence for SOC is 50%–90%,^6^ (3) MCAR missing data were included in the simulation and estimated to be 20% missing data in the outcome variable (PFP recurrence) and (4) α=0.05 (two tailed). Power analysis results showed power >0.80 if N=88 for analysis following missing data handling and the group (STRIPE vs SOC) term results in an OR>4.43.

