## Abstract

Patellofemoral pain (PFP) is a chronic condition that presents with patellar pain during various daily and recreational activities. Individuals with PFP have a wide range of impairments that result in long-term disability and reduced quality of life. Current interventions target hip muscle weakness with strength-based exercises, but recurrence rates are as high as 90%. A single feasibility study demonstrated success with power-based exercises; however, there is limited evidence evaluating pain or self-reported function in larger cohorts, and no study has assessed recurrence rates. This protocol details a study evaluating a strength-based rehabilitation programme compared with a strength-based programme incorporating power-based exercises in individuals with PFP. This single-blinded randomised controlled trial will evaluate 88 participants with PFP, aged 18–40 years old. Participants will be recruited from three universities, the surrounding community and sports medicine clinics. Participants will receive three telemedicine rehabilitation sessions a week for 6 weeks. The rehabilitation programme will consist of either strength-based exercises or a combination of power and strength-based exercises. Pain, subjective function and recurrence rates will be assessed at baseline, immediately after the intervention and at four follow-up time points: 6-month, 12-month, 18-month and 24-month postintervention. We will also assess neuromuscular function of the hips and global rating of change at each postintervention time point. Trial registration number NCT05403944.

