### Randomisation, blinding and treatment allocation

Participants will be assigned to a treatment group by block randomisation, with a computer-generated online research randomiser (http://www.randomizer.org), completed by the statistician ([name]) prior to study enrolment. We will use a four-block randomisation approach for each clinical site, to ensure equal groups across sites. The University of Connecticut site will enroll 44 participants, resulting in 11 equal blocks of randomisation. The University of Central Florida and University of Toledo will each collect 22 participants, resulting in five 4 blocks of randomisation and a final block of 2 participants to allow for equal randomisation. An additional four-block randomisation was provided for each site in the instance a participant was assigned to a group but dropped out before any study data were collected. Group assignment will be maintained with a master list and allocation concealed from the site-PIs.

The proposed study will include blinding the research members conducting the baseline and postintervention assessments from group allocation, while separate team members will perform all treatments and will not conduct baseline or postintervention assessments. The participants will not be blinded, as reviewing the informed consent will outline group differences. To control for selection bias, the randomisation will be completed by the statistician who will not be directly associated with data collection or intervention. Additionally, the statistician will oversee randomisation with concealed allocation in opaque envelopes that will only be opened after baseline testing. Participants will be assigned a random participant number per site, maintained in an encrypted and secure document by site-PIs, ensuring confidentiality. We will also collect numerous secondary variables, such as psychological factors, coping strategies, physical activity and lifestyle factors, which we aim to reduce bias by using them as covariates if they influence the primary outcomes.

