### Statistical analyses

We will use a MANCOVA to test for a significant treatment group (STRIPE vs SOC) main effect showing significantly greater improvement in each outcome variable at 6-week postintervention controlling for respective baseline values of each outcome variable. A multivariate intercept-only longitudinal SEM growth curve model will be used to determine if the difference in each outcome variable at 6-week postintervention is maintained at 6, 12, 18 and 24 months follow-up. The intercept-only SEM implies between-participant variability in the overall outcome variable, but the outcome does not change as a function of time. Finally, a binary logistic regression analysis will be used to determine if the intervention group (STRIPE vs SOC) significantly predicts PFP recurrence at the end of the 2-year follow-up. Dummy coded variables will be created and added to each analysis to account for cluster (site) differences and produce robust SEs. All missing data will be handled assuming MAR with maximum likelihood estimation consistent with currently accepted methodological research and practice.

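### The long-term growth curve model for pain, function and kinematics names no baseline score, although the 6-week analysis adjusts for it: precision is lost and the two results are on different footings

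*Protocol article*

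**What the plan says.** **6-week analysis.** Under Statistical analyses, the MANCOVA compares the groups while controlling for the baseline value of each outcome. The Sample size section assumes that these baseline scores explain "20% of 6-week postintervention variance" and reports power above 0.80 for d > 0.55.

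**Long-term analysis.** The next sentence of Statistical analyses turns to the follow-up: "A multivariate intercept-only longitudinal SEM growth curve model will be used" to judge whether the 6-week difference persists to 24 months. The Sample size section bases this model on "five 6-month assessment time points (postintervention, 6, 12, 18 and 24 months follow-up", so baseline is not one of the modelled visits. Its list of assumptions contains no baseline covariate and no baseline R². The result is: "Power analysis results showed power would be >0.70 for any (intercept) effect size difference between STRIPE and SOC participants of d>0.55".

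**Terms common to all analyses.** Statistical analyses adds site dummy variables to each analysis and names nothing else. The Randomisation section mentions further covariates if they prove influential. Those are psychological, coping, activity and lifestyle factors, not the baseline outcome score.

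**Availability.** Table 2 marks VAS, AKPS and single-leg-squat kinematics at baseline and at every later visit. Allocation envelopes are opened only after baseline testing.

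**The concern.** Two adjacent sentences specify two models for the same outcomes. One adjusts for baseline and the other, as written, does not. Two things follow.

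1. **Precision.** VAS and AKPS are primary outcomes measured to two years. A baseline score that correlates with later scores removes outcome variance at almost no cost. Without it, the long-term comparison has a wider standard error than it needs, and part of any chance baseline difference between arms of 44 stays in the estimate.
2. **Comparability.** The growth model is there to say whether the 6-week difference persists. If the 6-week difference is baseline-adjusted and the long-term one is not, an apparent loss or persistence could partly reflect the change in adjustment. The post-intervention visit belongs to both analyses, so the same data would be handled in two ways.

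**Working it through.** **Inputs from the protocol**
- Total N: "This single-blinded randomised controlled trial will evaluate 88 participants with PFP" (Abstract). Allocation is by blocks "to ensure equal groups across sites", hence 44 per arm. The growth-model paragraph does not restate N, so 88 is carried over.
- Test level: "α=0.05 (two tailed".
- SD = 1, from "standardisation of all outcome variables at all time points".
- d = 0.55; baseline R² = 0.20, stated for 6 weeks only.

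**Not given, so assumed:** the within-person correlation ρ over the five visits, and baseline R² at 6 to 24 months.

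**Step 1: unadjusted two-group approximation.** Noncentral t, with noncentrality δ = d / √(2/n):
- δ = 0.55 / √(2/44) = 0.55 / 0.2132 = 2.58; with 86 df, power = **0.72**. This agrees with the stated >0.70.

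**Step 2: add baseline.** The residual variance becomes 1 − R², so δ = 2.58 / √(1 − R²), with 85 df:

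| Baseline R² | δ | Power |
|---|---|---|
| 0 | 2.58 | 0.72 |
| 0.05 | 2.65 | 0.74 |
| 0.10 | 2.72 | 0.77 |
| 0.20 | 2.88 | 0.81 |

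The last row agrees with the >0.80 stated for the 6-week MANCOVA. The d detectable with 80% power is about 0.60 unadjusted and about 0.54 at R² = 0.20.

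**Step 3: does the agreement in Step 1 show why the figure is 0.70?** The planned model averages five visits. With d on the intercept scale, as the protocol's wording suggests, the variance of a person's five-visit mean is 1 + (1 − ρ)/(5ρ). At 44 per arm, ignoring missing data:

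| ρ | Variance | Power, no baseline | Power, baseline explains 20% of intercept variance |
|---|---|---|---|
| 0.5 | 1.20 | 0.64 | 0.72 |
| 0.7 | 1.09 | 0.69 | 0.77 |
| 0.9 | 1.02 | 0.71 | 0.80 |
| 1.0 | 1.00 | 0.72 | 0.81 |

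With d on the observed-score scale the variance is (1 + 4ρ)/5, and unadjusted power is 0.91, 0.83 and 0.76 at ρ = 0.5, 0.7 and 0.9. So a figure just over 0.70 fits an unadjusted model with high ρ, but it would also fit an adjusted model with ρ near 0.5. The number alone does not identify the cause. Baseline raises power in every row of the table.

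**Step 4: chance imbalance.** The standard error of the baseline difference is √(2/44) = 0.213 SD. With R² = 0.20, r = √0.20 = 0.447, so one standard error of imbalance moves the unadjusted estimate by 0.447 × 0.213 = 0.095 SD. At the 95% limit this is 1.96 × 0.095 = 0.19 SD, about a third of d = 0.55. With R² = 0.10 the one-standard-error shift is 0.316 × 0.213 = 0.067 SD.

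**The case against.** **A condensed article may leave the covariate list to the analysis plan.** This is fair in general, and nothing in the text forbids a baseline term. But the article does specify this model: it gives the visits, the simulation assumptions and the terms added to each analysis, and it states baseline adjustment for the neighbouring model. As written, baseline is absent. If the unseen plan already contains it, the remedy is one clarifying sentence.

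**The assumption that randomisation gives equivalent groups proves nothing.** This is correct. The MANCOVA makes the same kind of assumption and still includes baseline, so no weight is put on that wording.

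**A reader might infer that the omission explains the 0.70.** Steps 1 and 2 invite that, since R² alone moves 0.72 to 0.81 with N, d and alpha fixed. The documents do not support it as a finding. The two powers come from different simulations: six outcomes with 4.5% to 15.9% missing, against five visits with 1.1% to 9.1% missing. The within-person correlation is unstated, and >0.70 is only a lower bound.

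**A reader might also infer that the power can be restated as 0.81.** It cannot. The R² of 0.20 is given for 6 weeks and may be lower later. A two-group approximation should not replace a simulation of the planned model. At R² of 0.10 or less, the approximate power stays below 0.80.

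**A reader might think that the long-term result is biased, or that imbalance passes into it in full.** Neither holds. The unadjusted randomised comparison is unbiased, and at r of about 0.45 less than half of a standardised imbalance carries through. What is lost is precision and a like-for-like comparison.

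**Conclusion.** The concern stands as a correctable weakness of specification, not as an error that invalidates the analysis. As written, the long-term model for VAS, AKPS and kinematics leaves out a covariate that is already collected before allocation and already used at 6 weeks. In the two-group approximation at d = 0.55 and N = 88, adding it raises power from about 0.72 to between 0.74 (R² = 0.05) and 0.81 (R² = 0.20). The exact gain depends on the long-term baseline R² and the within-person correlation, and the protocol gives neither. Separately from power, the question of persistence should be answered with both estimates adjusted in the same way. The stated >0.70 is consistent with an unadjusted analysis; its cause is not documented.

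**What to change.** 1. In Statistical analyses, prespecify the baseline value of each outcome (VAS, AKPS and each kinematic measure) as a predictor of the intercept in the longitudinal model, beside the site indicators. Fix this before any unblinded analysis.
2. Rerun the growth-model power simulation with the baseline term. State N, the within-person correlation and the scale of d, and show the result over a range of long-term baseline R², for example 0.05 to 0.20. Report what the simulation gives rather than the approximation shown here.
3. If the analysis plan already includes baseline in this model, say so in the protocol and confirm whether the stated power reflects it.

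The cost is one covariate per outcome, one sentence and one rerun of the simulation, with no new data or visits. The extra parameters in a multivariate model with 88 participants are a small cost, and the rerun will show whether they matter.
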